##### Practical aspects of the research

- - 1. Informed consent

It will be obtained after information during the pre-anaesthetic consultation or during the final pre-anaesthetic visit, by one of the investigator(s). The patient will receive the information form and will be asked to sign the consent form in triplicate, after a reasonable period of reflection.

- - 1. Devices used for anesthesia

General anesthesia is induced and maintained by propofol and remifentanil.

- Propofol is administered in both arms by an intravenous anesthesia system with a pK/pD concentration target: Primea Orchestra® base (Fresenius) used routinely in the department.
- Remifentanil is administered
  - in the "*standard practice"* arm, by an intravenous anesthesia system with a concentration target based on a pK/pD model: Primea Orchestra® base (Fresenius) used routinely in the department. Authorized targets according to standard practice range from 0.0 to 10.0 ng.ml^-1^ during anesthesia.
  - In the *ANI-loop* arm, remifentanil is automatically administered by the ANI-loop medical device.
    1. Anesthesia procedure

*Welcoming patients to the operating room*

Installation of standard monitoring equipment

ECG, plethysmography, non-invasive blood pressure (NIBP), entropy, ANI.

Collection of usual hemodynamic constants and calculation of HR thresholds_bl_ and PAS_bl_ used in intra-anaesthesia.

Randomization directly via electronic CRF and allocation to *"standard practice"* or *"ANI-loop"* arm.

The Physiodoloris® monitor (ANI index) remains visible in both study arms.

*Induction of anesthesia*

Similar anesthetic induction in both groups: midazolam 0.08 mg.kg^-1^ IVD

remifentanil target set at 8.0 ng.ml^-1^

propofol target set at 5.0 µg.ml^-1^ then increased in 1 µg.ml increments^-1^ until loss of consciousness.

Tracheal intubation, possibly after curarization

propofol and remifentanil targets lowered to 3 µg.ml^-1^ and 3 ng.ml respectively^-1^

Controlled Assisted Ventilation (CAV): tidal volume of 8 ml.kg^-1^ of ideal weight, ventilatory frequency: 12 cycles.min^-1^

Tidal volume will be adapted to maintain FetCO2 in the range [30 - 35 mmHg].

*Maintenance of anesthesia during the procedure*

- propofol target adapted in both arms to maintain the hypnotic component index (BIS® or Entropy®) in the range [40-60]. During *the procedure*, propofol target changes will be made 1 minute after the last target change has become effective, and will follow the indications in table 1. This corresponds to the usual management in the burn unit of the Burn Treatment Center.

|  |  |  |
| --- | --- | --- |
| component  hypnotic | propofol target |  |
| >80 | + 2.0 |  |
| >60 | + 1.0 |  |
| <40 | - 0.5 |  |
| <25 | - 1.0 |  |
| **Table 1: Adaptation of propofol targets in both arms** | | |

|  |  |  |
| --- | --- | --- |
| ANI | target remi |  |
| <35 | + 2.0 |  |
| <50 | + 1.0 |  |
| >70 | - 0.5 |  |
| >90 | - 1.0 |  |
| **Table 2: Adaptation of remi targets in the "standard practice" arm** | | |

- remifentanil target
  - **in the *standard practice* arm**: increased to 4 ng.ml-1 at the start of *the procedure*, then adjusted to maintain ANI in the range [50-70] as indicated in Table 2. Target changes are made 1 minute after the last target change has become effective. This corresponds to usual management at the Burn Treatment Center.
  - **in the *ANI-loop* arm**, the automatic mode of the ANI-loop device is engaged at the start of *the procedure*. The flow of remifentanil is automatically regulated by the ANI-loop. The anaesthetist can switch to manual mode at any time in the event of inadequate regulation (device disengagement). The device is switched off at the end of the *procedure.*

Pre-emptive analgesia

- local infiltration of skin sample area with naropein 2 mg.ml-1 during

*intervention*

- paracetamol 1g IVL at end of *procedure*
- sufentanil 0.12 µg.kg-1 (max 10 µg) IVL at *end of procedure*

Prevention of postoperative nausea/vomiting

- ondansetron 4 mg IVL

Postoperative analgesia

- morphine titration according to Visual Analogue Scale (VAS), bolus of 3mg every 3 min (max 12mg)
- ketamine 20 mg IVL for persistent pain with VAS ≥ 40

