##### Secondary objectives and hypotheses

To determine whether the automated administration of remifentanil by the ANI-loop device allows:

- improving hemodynamic stability during propofol general anesthesia.
- increasing the time spent with an ANI between 50 and 70.
- reducing immediate post-operative pain.

In the *"ANI-loop*" arm only: determine whether ANI-loop enables fully automated administration (i.e. without the need to disengage the device).

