##### Evaluation criteria

- - 1. Definitions
- *baseline" values* for heart rate (HRbl) and systolic blood pressure (SBPbl) are the mean of 3 measurements taken before the start of anesthesia
- *hemodynamic reactivity*: HR > 120% of HRbl or SBP > 120% of SBPbl
- *hypotension*: PAS <75 mmHg
- *bradycardia*: HR < 40 min-1
- *intervention*: begins with skin preparation, includes surgery and ends with the end of dressing
  - 1. main criterion, making it possible to meet the main objective

Total quantity of remi administered (value related to weight and duration of intervention).

- - 1. secondary criteria to meet secondary objectives:

NB: several criteria are assessed after the patient wakes up, between extubation (H0) and H2 120 min after extubation. The patient does not need to be in the intensive care unit for this assessment; he/she can be in his/her hospital room.

- Proportion of time spent in hemodynamic reactivity, hypotension or bradycardia during the procedure. This proportion will be equal to the cumulative duration of each episode of reactivity, hypotension or bradycardia, divided by the duration of the procedure Total dose of Ephedrine.
- ANIi and ANIm: proportion of time spent during the intervention in the following intervals :

<50, [50-70], >70

- hypnotic component measurement index (BIS® or Entropie®): proportion of time spent during the procedure in the following intervals: <40, [40-60], >60
- ANI, heart rate, blood pressure, FetCO2, Pmax (ventilator) 5 min before start of procedure, 5 min after start of procedure and 20 min after start of procedure.
- Pain assessed by visual analog scale (VAS) between H0 and H2, every 15 min.
- Total quantity of morphine administered between end of surgery and H2 post-op.
- Total quantity of ketamine administered between end of surgery and H2 post-op.
- Frequency of postoperative nausea/vomiting assessed at H2.
- Number of changes in remifentanil flow rate during the procedure.
- Total quantity of propofol administered (absolute value, value related to weight, value related to weight and duration of procedure).
- Number of propofol target changes during the procedure.

In the *"ANI-loop"* arm only: number and total duration of disengagements of the ANI-loop device during the operation, i.e. the number of times and cumulative duration that the closed-loop system had to be interrupted and replaced by manual control, as in the standard practical arm.

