##### Analysis method and strategy

Statistical analyses will be carried out using SAS software (version 9.4 or higher) at the Lille CHRU's methodological support platform, under the responsibility of [name]. All statistical tests will be two-sided, with a first-species risk of 5%. No intermediate analyses are planned. A detailed statistical analysis plan will be drawn up and validated before the database is frozen.

Patient characteristics at inclusion will be described for each of the two study arms. Qualitative variables will be described by numbers and percentages. Quantitative variables will be described by the mean and standard deviation in the case of a Gaussian distribution, or by the median and interquartile range (i.e. 25th and 75th percentiles) in the opposite case. The normality of distributions will be tested by a Shapiro-Wilk test and verified graphically by histograms.

Primary objective: The total amount of remifentanil administered (value related to weight and duration of intervention) will be compared between the two arms of the study by a Student's t-test; the effect size will be calculated (standardized mean difference) with a 95% confidence interval. If the distribution of the primary endpoint deviates from normality, the Mann-Whitney U test will be used.

Secondary objectives: Qualitative secondary endpoints will be compared between the two arms of the study using a Chi-square test or Fisher's exact test (when the validity conditions of the Chi-square test are not met). Quantitative secondary endpoints are compared between the two arms of the study using a Student's t-test, or a Mann-Whitney U-test if the distribution of the endpoint deviates from normality. Quantitative secondary endpoints measured at different times will be compared between the two arms of the study using a linear mixed model. This model takes into account the correlation between repeated measurements in the same patient, and the possible existence of missing data. The choice of correlation model will be based on the AIC criterion. The validity of the model will be studied by analyzing the residuals. In the event of significant deviations from normality without obvious transformation of the criterion, the criteria will be compared at each time point between the groups using Mann-Whitney U tests. Finally, secondary criteria identified only in the

The "*ANI-loop*" model will be described using the usual descriptive statistics.

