#### Data processing and storage of documents and research data

Data processing will be carried out under the conditions of confidentiality defined by the French Data Protection Act of January 6, 1978 (CNIL). Data processing will be carried out in accordance with the requirements of CNIL reference methodology MR 06001.

In order to best meet the objectives of this study, all the variables will be drawn up in collaboration with the investigator, the datamanager and the biostatisticians.

The paper CRF will then be formatted to organize the data and enable logical collection according to the patient pathway or location of the data to be collected.

The final version of the CRF will be validated by the investigator, the datamanager and the biostatisticians.

This final version will be used to develop an eCRF by [name]'s Unité de Méthodologie, Biostatistiques et Datamanagement at the Lille CHRU.

The eCRF will be developed on Ennov Clinical, which is FDA-approved and offers optimal database quality.

This eCRF will enable on-the-fly tests to be carried out in relation to the expected data dictionary, as well as data consistency tests. These tests will be defined by the investigator and the data manager prior to the development of the input mask.

Final data monitoring, defined by the consistency tests set up, will be carried out to check the consistency and quality of the data entered.

Data will be collected directly on the eCRF. Patient anonymization will be managed outside the eCRF.

The center must hold the list of patient identifier/identity correspondences in a secure manner that is inaccessible to people who do not have consultation rights. These identifiers will be transferred to the eCRF.

Data will be hosted at the CHRU in Lille, via our partner eSIS (Groupement d'Intérêt Public named GIP e-SiS 59/62).

Data concerning this study will be archived for a minimum period of fifteen years from the end of the research or its early termination, without prejudice to the legislative and regulatory provisions in force.

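### The protocol schedules no pain score and no record of opioid use before randomisation, so the post-operative pain comparison may lose precision that would be cheap to gain

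*Protocol*

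**What the plan says.** The protocol's secondary objectives (section 3.2) include "reducing immediate post-operative pain". Under Evaluation criteria (section 4.3) this is measured by "Pain assessed by visual analog scale (VAS) between H0 and H2, every 15 min", where H0 is extubation: "several criteria are assessed after the patient wakes up, between extubation (H0) and H2 120 min after extubation". A related criterion is "Total quantity of morphine administered between end of surgery and H2 post-op", with a parallel one for ketamine.

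The only defined baseline values are heart rate and systolic pressure, which "are the mean of 3 measurements taken before the start of anesthesia". The step on arrival in the operating room (section 5.2, Anesthesia procedure) matches this. It lists the monitoring to be installed and "Collection of usual hemodynamic constants and calculation of HR thresholds", with the corresponding pressure threshold, and then randomisation. No eligibility criterion concerns existing pain or opioid treatment.

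Under Analysis method and strategy (section 4.5), single-value quantitative secondary criteria are compared by Student's t-test or Mann-Whitney test, and repeated ones by a linear mixed model. No baseline term is named. Baseline data are covered in general terms: "Patient characteristics at inclusion will be described for each of the two study arms". The section on data processing leaves the content of the case report form open: "all the variables will be drawn up in collaboration with the investigator, the datamanager and the biostatisticians".

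**The concern.** All participants are burn patients having excision-grafting. Some may plausibly arrive in pain or already taking opioids, though the documents neither say so nor say how often. A patient's pain and opioid exposure before surgery can be expected to influence the VAS after it. Because post-operative morphine is titrated to VAS, they can influence the morphine total as well. Without a baseline reading, that between-patient variation stays in the error term, and a chance difference between arms cannot be seen or adjusted for.

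Timing makes this a protocol matter. A covariate can be named in the statistical analysis plan, which need only be validated before the database is frozen. A pain score not taken before induction cannot be recovered by then. The opportunity exists: unconscious or sedated patients are not included, so at this step the patient is awake, has consented and has not yet been allocated.

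**Working it through.** **The plan's own figure.** Inputs from section 4.4: control mean 0.30, SD 0.075, experimental mean 0.24, two-sided alpha 5%, power 80%. The standardised effect is 0.06 / 0.075 = 0.8. The normal approximation gives 25 per arm. The exact noncentral-t calculation gives power of 79.15% at 25 and 80.75% at 26, so 26 per arm and 52 in total reproduce. This concerns remifentanil quantity only; no SD, effect or power is stated for VAS or morphine.

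**Inputs for the pain comparison.** From the protocol: 26 per arm, two-sided 5%. Assumed: correlation r between pre- and post-operative VAS, shown at 0.3 and 0.5. Results are in SD units of a single post-operative value per patient, a simplification of the repeated-measures model, and ignore the one degree of freedom spent.

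**Detectable difference at 80% power.**
- Unadjusted: (1.960 + 0.842) × √(2/26) = 2.802 × 0.2774 = 0.78 SD.
- Adjusted: multiply by √(1 − r²).

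| r | Variance removed (r²) | Detectable difference | Power for an assumed 0.5 SD effect | Equivalent unadjusted total, 52/(1 − r²) |
|---|---|---|---|---|
| 0 | 0% | 0.78 SD | 44% | 52 |
| 0.3 | 9% | 0.74 SD | 47% | 57 |
| 0.5 | 25% | 0.67 SD | 55% | 69 |

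**Chance imbalance.** The standard error of the between-arm difference in baseline VAS is √(2/26) = 0.277 SD.
- Gap above 0.3 SD: 0.3 / 0.277 = 1.08, two-sided probability 28%.
- Gap above 0.5 SD: 0.5 / 0.277 = 1.80, two-sided probability 7%.

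With a linear relation, a 0.3 SD baseline gap moves the unadjusted post-operative difference by r × 0.3: 0.09 SD at r = 0.3 and 0.15 SD at r = 0.5.

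For prior opioid use (yes/no), an assumed prevalence of 20% to 50% gives a probability of 6% to 13% that the arms differ by at least 20 percentage points.

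**The case against.** The strongest reply is that this is an inference from silence. The protocol lists none of its inclusion characteristics and defers the case report form, and the heart rate and pressure step serves intra-operative thresholds rather than acting as a full baseline list. A reader might conclude that neither item is collected. The documents do not support that; they show only that the protocol does not provide for it. The deferred form could include both items, but nothing ensures that it will.

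Second, covariates are commonly left to the statistical analysis plan, and the fixed effects of the mixed model are not listed. That stands for the choice of model terms. It does not answer the missing reading, which no later plan can supply.

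Third, a reader might infer that the loss is irreversible for both items. Opioid intake can probably be retrieved: patients are treated in the same centre, are seen before anaesthesia, and have clinical files open as source data. Only the VAS reading is perishable.

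Fourth, the gain depends on r. Post-operative pain is actively treated and grafting adds a donor site, which may weaken the link to pre-operative pain. At r = 0.3 the gain is small (power for a 0.5 SD effect moves from 44% to 47%). This is why the range stops at 0.5 and no figure is claimed for morphine.

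**Conclusion.** The point holds as a cheap improvement to one secondary objective, of minor to moderate weight. The protocol specifies neither a pre-operative VAS nor prior opioid use, and the VAS reading is lost once the patient is induced. On an assumed correlation of 0.3 to 0.5, adjustment would remove 9% to 25% of the variance and bring the detectable difference from 0.78 SD to between 0.74 and 0.67 SD. If the true correlation is near zero, the gain in precision disappears.

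Two stronger readings should be resisted. A reader might infer that the pain results would be biased. Randomisation leaves any imbalance to chance, so the unadjusted tests remain valid. A reader might also take imbalance to be likely. The calculated probability is about 28% for a gap above 0.3 SD and 7% above 0.5 SD. That pre-operative pain or opioid use matters more than the way remifentanil is delivered has no support in the documents. The primary endpoint and its sample size of 52 are untouched.

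**What to change.** In section 5.2 (Anesthesia procedure, arrival in the operating room), add before randomisation a resting VAS, and opioid intake over the previous 24 hours taken from the patient or the medical record. In section 4.5, enter baseline VAS as a covariate in the linear mixed model for post-operative VAS. Present any baseline-adjusted morphine comparison as supportive only, with its model to be specified in the statistical analysis plan.

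The cost is about a minute per patient, two fields in the electronic case report form and one model degree of freedom. Treatment, eligibility and sample size do not change.

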##### Duration

The sponsor reserves the right to discontinue the trial in the event of non-inclusion. The study may be stopped by a joint decision of the competent authority, the sponsor or the principal investigator.

- duration of inclusion period: 12 months
- duration of study participation for one subject: from arrival in the OR to H2 post-op.
- duration of research: 15 months
- data analysis time: 3 months

##### Criteria for discontinuing study participation

Each subject may leave the study by decision of the competent administrative authority, the sponsor and the principal investigator, but also by decision of an investigator or by decision of the subject him/herself, in accordance with the regulations and as mentioned in the consent form.

- the presence of a major extrasystole (more than two extrasystoles per minute without interruption) is a criterion for stopping a patient's participation in the study, because ANI measurements are not possible under these conditions.
- In this case, the patient's inclusion would be deemed null and void; the investigating center would then proceed with an additional inclusion in replacement.
- no follow-up of the excluded patient is justified by participation in the study.

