##### Definition of the study population

The ANI measurement provided by the PhyioDoloris monitor cannot be interpreted in several situations. All the criteria concerned are taken into account in the non-inclusion or exclusion criteria;

- arrhythmia
  - Exclusion criteria
- absence of breathing (e.g. apnea due to intubation)
  - Not applicable; the ANI-loop device is not used in automatic mode when the patient is not intubated and mechanically ventilated.
- respiratory rate below 9 cycles/min
  - Not applicable; the protocol provides for a respiratory rate of 12 minute cycles.
- current volume variable over the measurement time, i.e. 64 seconds
  - Not relevant; for this type of anaesthesia, tidal volume adjustments are usually made at most 1 to 2 times per hour. Significant changes in

tidal volume over a period of 64 seconds are not used in this clinical context.

- irregular breathing (when talking, laughing or coughing)
  - Not applicable; the ANI-loop device is not used in automatic mode when the patient is not intubated and mechanically ventilated.
- pace maker (certain types)
  - Non-inclusion criteria
- heart transplantation
  - Non-inclusion criteria
- Use of drugs affecting cardiac sinus activity (Atropine...)
  - Excusion criteria; atropine injections(parasympatholytic) andpropranolol (sympatholytic)
    1. Inclusion criteria
- patients treated at the Lille CHRU Burn Treatment Centre
- burn surgery: excision-grafting
- age ≥ 18 years
- informed consent
- ASA I or II or III status
- general anaesthesia with intubation and controlled assisted ventilation
- body mass index between 17 and 40 kg.m-2
  - 1. Non-inclusion criteria
- pregnant or breast-feeding women (simple questioning)
- pace maker (regardless of operating mode)
- heart transplantation
- non-sinus rhythm
- dysautonomia
- diabetes mellitus with micro or macro angiopathic complications
- foreseeable allergy or intolerance to a drug used in the study
- baseline" hemodynamic measurements considered as hypotension or bradycardia
- FCbl>120 min^-1^ or PASbl>160 mmHg
- uninsured
- persons deprived of their liberty, in emergency situations, or persons incapable of consent and not benefiting from a legal protection regime (guardianship/curatorship)
- unconscious or sedated patient before induction

NB: There is no pregnancy test to check this criterion; it will be a simple questioning.

- - 1. Exclusion criteria
- Arrhythmia

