- significant extrasystole (more than two extrasystoles per minute without interruption during surgery)
- Intraoperative atropine injection
- Intraoperative injection of propranolol.

If a patient is excluded, his or her inclusion is deemed null and void; the investigating center will then proceed with an additional inclusion in replacement. No follow-up of the excluded patient is justified by participation in the study.

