##### Calculating the number of subjects

The aim of the study was to assess whether the ANI-loop medical device could reduce the total amount of remifentanil (remi) administered compared with standard practice. Based on literature data [Leal PC et al.] and the department's usual practice, the total amount of remifentanil in the control group can be estimated at 0.30 ± 0.075 (mean ± standard deviation). To demonstrate a 20% reduction in the *ANI-loop* arm (i.e., a mean remifentanil quantity of 0.24 in the experimental group), with a first-species risk of 5% and a power of 80%, we need to include 26 patients per group, for a total of 52 patients.

Reference:Leal PC, Sakata RK, Salomão R, Sadatsune EJ, Issy AM. Braz J Anesthesiol. 2013 Mar- Apr;63(2):178-82.

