#### ANI_a_ <ANI :_min_

In this area, we consider that analgesia is insufficient. This event is treated by increasing the infusion pump rate.

**If(**InF<InFmax)**and**(S_a_ <SaT) **then** InF = InF+InI (4)

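### Events that make ANI unusable void the patient, but the protocol never states the status of the ANI-driven loop at that moment, and the events drop out of the disengagement criterion

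*Protocol*

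**What the plan says.** **When ANI fails.** Protocol 4.2 lists situations in which ANI cannot be interpreted and says that the non-inclusion or exclusion criteria cover them all. For apnoea and irregular breathing it adds that the loop is not in automatic mode at such times. For arrhythmia and for drugs acting on the sinus node (atropine, labelled parasympatholytic, and propranolol, labelled sympatholytic) it says only that they are exclusion criteria.

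**Consequence.** Section 4.2.3 lists arrhythmia, sustained extrasystoles, "Intraoperative atropine injection" and propranolol. An excluded patient's inclusion is void, a replacement is recruited, and the study requires no follow-up. Section 5.4 repeats this for extrasystoles, "because ANI measurements are not possible under these conditions". Neither section mentions the infusion in progress.

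**The loop.** Under 5.2.3, automatic mode is engaged at the start of the procedure and the device is switched off at its end. In between, the anaesthetist may go to manual mode at any time if regulation is inadequate.

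**The algorithm.** When average ANI is below 50, Appendix I states: "In this area, we consider that analgesia is insufficient. This event is treated by increasing the infusion pump rate". Its only automatic shutdown is for systolic pressure below 80 mmHg. Below 90 mmHg the flow goes to its minimum.

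**The outcomes.** Section 3.2 asks whether the loop can run fully automatically. Section 4.3 measures this, in the ANI-loop arm only, by the number and total duration of disengagements.

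**The concern.** All four triggers arise during surgery, after randomisation and possibly with the loop running. For at least arrhythmia, extrasystoles and atropine, the protocol's reason for exclusion is that the control signal has become unreliable. It then says what happens to the patient's data and not what happens to the controller that acts on that signal.

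Two things are at stake. The first is safety: the algorithm as written has no condition that recognises the failure, so everything depends on the anaesthetist's optional switch. The second is statistical. Loss of a usable ANI is a plain way for an ANI-driven loop to fail at full automation, and the voiding rule removes exactly those patients from the criterion meant to measure it.

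**Working it through.** **The plan's own figures.** The sample-size section aims "To demonstrate a 20% reduction in the *ANI-loop* arm": 0.30 × 0.80 = 0.24, SD 0.075, difference 0.06. The normal approximation gives 2 × (1.960 + 0.842)² × (0.075/0.06)² = 24.5, so 25 per arm. The t-test version gives 25.5, so 26 per arm with power 0.807. The stated 26 is reproduced. This point does not depend on it, but 0.24 and 26 are used below.

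**Direction of the ANI error.**
- Atropine: Appendix II describes ANI as the relative amount of parasympathetic tone, and 4.2 calls atropine parasympatholytic. A low ANI follows. In the Appendix I formula, ANI = 100 × (5.1 × AUCmin + 1.2)/12.8. With AUCmin = 0 this is 120/12.8 = 9.4, far below the threshold of 50.
- Arrhythmia and extrasystoles: the documents say only that ANI is uninterpretable or not measurable. Appendix I describes filtering that replaces disturbed RR samples. No direction is given.
- Propranolol: no direction is given either.

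**What rule (4) does with a low, flat ANI.** Inputs from Appendix I: increment 0.01 µg/kg/min, refractory period 10 s, ceiling 0.6, minimum 0.05, slope threshold 7. As printed, the rule fires if flow is below the ceiling and the ANI slope is below +7. A slope of 0 meets this, so the flow can rise by one step every 10 s.
- From 0.05: (0.60 − 0.05)/0.01 = 55 steps × 10 s = 550 s = 9.2 min.
- From 0.24: (0.60 − 0.24)/0.01 = 36 steps × 10 s = 360 s = 6.0 min.
- Between two cuff readings 2.5 min apart: 150/10 = 15 steps, or +0.15 µg/kg/min.

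The flow at onset is not given. The value 0.24 is the planned mean in the loop arm, and the protocol prints it without a unit; µg/kg/min is assumed.

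**The opposite error.** If ANI read falsely high (above 75) and rising, rule (7) would lower the flow, for example from 0.30 to 0.06 in 24 steps, or 4.0 min. The upward drift therefore cannot be extended to the rhythm triggers.

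**Effect on the automation result.** The protocol gives no event frequency, so this is an illustration. Suppose that all 26 analysed loop patients run without disengagement and that 1, 2 or 3 others were voided for an ANI failure and replaced in the same arm. The reported share fully automated is 26/26 = 100%. With the voided patients counted as failures it is 26/27 = 96.3%, 26/28 = 92.9% or 26/29 = 89.7%. The error favours the device in every case.

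**The case against.** The strongest reply is that this is a silence and that the natural reading fills it. Ending participation can be taken to end use of the study device, since the synopsis says the arms differ only in how remifentanil is given. The loop is supervised throughout, manual mode is available at any time, the risk section says disengagement is possible without delay, and the software allows shutdown. Atropine is given by the attending team, so minutes of unattended upward drift are least plausible for the one trigger whose direction is known. Adverse events and protocol deviations must still be recorded. The control arm also follows ANI, through Table 2, so the gap is not unique to the device, although there each change is made by hand.

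Much of this stands. A reader might infer that the protocol orders the loop to run on after exclusion, that all the triggers drive remifentanil up, or that the rise is unchecked. The documents support none of these. No sentence keeps the loop engaged after exclusion. The direction is known for atropine only. The rise is bounded by the 0.6 ceiling, by the systolic-pressure rules and by the anaesthetist.

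The reply leaves two things unanswered. Section 4.2 does state the device mode for apnoea and irregular breathing, so its absence for the intraoperative triggers is an unevenness within the same list. And adverse-event or deviation records do not put a voided patient back into the disengagement criterion.

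**Conclusion.** The point holds as an unreconciled gap, not as a flat contradiction. The exclusion sections declare the signal unusable and void the patient. The procedure section leaves automatic mode on until the end of the procedure, subject to an optional switch, and Appendix I contains no stop for rhythm, drug or ANI validity.

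For atropine, the worst case is a rise to the ceiling in about 9 min from 0.05, or about 6 min from 0.24. This assumes that average ANI stays below 50, that rule (4) applies as printed, that systolic pressure stays at 90 mmHg or above, that nobody intervenes, and, for the second figure, that the unit is µg/kg/min. For arrhythmia, extrasystoles and propranolol no size or direction can be given.

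The firmer statistical consequence is the bias in the automation objective. Its direction is known, in favour of the device. Its size depends on an event frequency that the protocol does not state.

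**What to change.** 1. Reconcile sections 4.2, 4.2.3, 5.2.3 and 5.4 with Appendix I so that the status of automatic mode at each exclusion event is stated once and consistently. Which clinical rule applies is for the investigators.
2. In the ANI-loop arm, log the time of each such event and the remifentanil flow at that moment.
3. Count these events in the disengagement criterion of 4.3, including those in patients later excluded. The voiding clause needs a matching exception so that the data up to the event are kept for this purpose.

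The cost is protocol and appendix wording, one log field, and a slightly less favourable automation result.
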